**Trial registration number:**

NCT07355179.

STRENGTHS AND LIMITATIONS OF THIS STUDYCluster-randomised trial design conducted in real-world kindergarten settings, enhancing ecological validity and relevance for early childhood education practice.Affordance-based, co-created intervention, developed with children and supported by educator training, addressing both environmental and pedagogical determinants of physical literacy.The limited number of clusters may constrain statistical power and generalisability at the cluster level, despite an adequate individual-level sample size.The context-specific nature of outdoor kindergarten environments may limit transferability to settings with different spatial, cultural or pedagogical characteristics.Outdoor-based physical activity assessments may be influenced by seasonal and weather-related variability, potentially affecting interpretation of movement-related outcomes.

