## Methods and analysis

### Study design

This study is a cluster-randomised trial, with randomisation at the kindergarten (KG) level, to be conducted in public preschools in Évora, Portugal. The trial includes three KG (clusters). One cluster (four classrooms) is being used in an initial pilot phase to assess feasibility, acceptability and implementation procedures. Following the pilot phase, the intervention will be implemented in the remaining two clusters (three classrooms each), with one assigned to the intervention condition and the other serving as a wait-list control group. The study follows a preintervention and postintervention assessment design. After the pilot phase, the two remaining KG will be randomised at the cluster level in a 1:1 ratio, with one allocated to the intervention group and the other to the wait-list control group. The random allocation sequence will be generated by an independent researcher not involved in recruitment, intervention delivery or outcome assessment, using a computer-generated randomisation procedure. Given the small number of clusters, simple randomisation will be used. The allocation will then be communicated to the research team responsible for implementing the intervention.

The initial pilot phase involves approximately 75 children from one KG, designed to assess the feasibility, acceptability and implementation procedures of the PLAY UP intervention.

The study commenced in January 2026 with recruitment and is currently ongoing, with completion scheduled for the end of June 2027. The intervention phase will consist of 15 sessions per classroom delivered over approximately 8–10 weeks, followed by postintervention assessments. The main comparative study phase will be implemented after completion of the pilot phase, following the same procedures.

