### Sample size

The protocol includes an initial pilot phase involving approximately 75 children to assess feasibility, acceptability and implementation procedures.

For the main comparative phase, sample size was estimated using G*Power (F tests: analysis of variance repeated measures, within–between interaction). Assuming a moderate effect size (f=0.25), α=0.05, power=0.80, two groups, two measurement occasions (baseline and postintervention), a correlation among repeated measures of 0.50 and ε=1, the required total sample size was 34 children.

The overall recruited sample exceeds this individual-level requirement. Given the study design and the limited number of KG clusters in the comparative phase, findings related to intervention effects will be interpreted with caution, and effect estimates with CIs will be reported to support interpretation and inform future sample size assumptions.

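### The 34-child, 80%-power calculation assumes independent children, but the comparison randomises one kindergarten per arm, so that power cannot be claimed for this design

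*Protocol article*

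**What the plan says.** On design, the protocol article (Study design) states: "This study is a cluster-randomised trial, with randomisation at the kindergarten (KG) level". Of three kindergartens, one is used for the pilot. For the comparative phase, "the two remaining KG will be randomised at the cluster level in a 1:1 ratio", which means one kindergarten per arm. Each of the two has three classrooms: "the intervention will be implemented in the remaining two clusters (three classrooms each").

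On sample size, for the main comparative phase, "sample size was estimated using G*Power (F tests: analysis of variance repeated measures, within–between interaction"). The inputs are given as: "Assuming a moderate effect size (f=0.25), α=0.05, power=0.80, two groups, two measurement occasions (baseline and postintervention"), with a correlation of 0.50 between occasions and ε=1. The result is that "the required total sample size was 34 children". No ICC, design effect or cluster term enters. The section then judges the requirement met: "The overall recruited sample exceeds this individual-level requirement". It adds that, because there are few clusters, effects will be read cautiously and reported with confidence intervals.

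The strengths and limitations list says that the few clusters may limit power at cluster level, "despite an adequate individual-level sample size". The Abstract says that the analysis will use cluster-aware models.

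**The concern.** The power calculation and the design describe different experiments. The calculation gives each child an independent contribution to the treatment comparison. In the trial, all children in an arm share one kindergarten, with its staff, outdoor space and routines, and any kindergarten-level difference in change over time is indistinguishable from the intervention effect.

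The 80% figure and the word adequate are the only quantitative support offered for the comparison on the primary outcome, motor competence. If they stand, results can be misread in both directions. A null result may be taken as well powered. A significant result may be taken as evidence for the intervention when ordinary differences between two kindergartens could produce it. The second risk is at least as serious as the first.

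The comparator is also wrong. The requirement is for the main phase, but it is set against the whole recruited sample, which includes the pilot kindergarten.

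**Working it through.** **Inputs from the protocol.** f=0.25, α=0.05, power 0.80, two groups, two occasions, correlation ρ=0.50, ε=1 (Sample size). Total recruited 215 (Recruitment). Pilot about 75 children in one kindergarten (Study design), analysed separately from the main phase (Data analysis). Two kindergartens with three classrooms each in the main phase (Study design).

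**Assumptions.** An equal split between the two kindergartens, no dropout, and an ICC of the change score between 0.01 and 0.10. The protocol gives no ICC.

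**1. Reproducing 34.** Noncentrality λ = f²·N·m/(1−ρ), with m=2 occasions. For N=34, λ = 0.0625×34×2/0.5 = 8.5 on F(1, 32), giving power 0.807. For N=32, λ = 8.0 and power is 0.781. So 34 is the smallest even total that reaches 0.80. The arithmetic is correct for independent children.

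**2. Planned effect on the change scale.** With ρ=0.50, the SD of change is √(2×(1−0.50)) = 1.0 outcome SD. For two equal groups λ = (N/4)·d², so d² = 8.5×4/34 = 1 and d = 1.0 SD of change.

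**3. The right comparator.** 215 − 75 = about 140 main-phase children, or about 70 per kindergarten. Because 140 also exceeds 34, using 215 does not by itself alter the comparison. With 140 independent children the nominal power would exceed 0.999.

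**4. Degrees of freedom.** With two kindergartens in two arms, between-kindergarten df = 2 − 2 = 0. The between-kindergarten variance cannot be estimated from the comparison. A permutation test over the two possible allocations has a smallest two-sided p-value of 2/2 = 1.0.

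**5. Optimistic case: ICC treated as known.** DE = 1 + (70−1)×ICC; effective N = 140/DE; inflated requirement = 34×DE. Power uses the step 1 formula at the effective N.

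| ICC (assumed) | DE | Effective N | Required N | Power |
|---|---|---|---|---|
| 0.01 | 1.69 | 82.8 | 57.5 | 0.99 |
| 0.02 | 2.38 | 58.8 | 80.9 | 0.97 |
| 0.05 | 4.45 | 31.5 | 151.3 | 0.77 |
| 0.10 | 7.90 | 17.7 | 268.6 | 0.51 |

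Break-even ICC = (140/34 − 1)/69 = 0.045.

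**6. Type I error if kindergarten is ignored.** With 70 children per arm, the true variance of the difference in mean change is 2·ICC + 2(1−ICC)/70, while the test uses only 2(1−ICC)/70. Simulated two-sided error at nominal 0.05 is about 0.13, 0.21, 0.36 and 0.51 at ICC 0.01, 0.02, 0.05 and 0.10.

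**7. Classrooms as units.** Three per arm gives 4 df, with 140/6 = 23.3 children per classroom. The SE of the difference is √(2×(ICC + (1−ICC)/23.3)/3), which is 0.246 at classroom ICC 0.05 and 0.304 at 0.10. By noncentral t, the difference detectable with 80% power is about 0.92 SD and 1.14 SD of change, against the planned 1.0 SD. This holds only if there is no between-kindergarten variance.

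**The case against.** The strongest reply is that the protocol claims little. It calls 34 an individual-level requirement, and the sentence comparing it with the recruited sample is literally true for 215 and for 140. Both places where adequacy is mentioned carry a warning about few clusters, and one promises cautious interpretation with confidence intervals. By design effect alone, power is 0.97 or more at ICC 0.01 and 0.02, so a shortfall depends on a value the protocol does not give.

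Much of this stands, and it rules out several stronger readings that a reader might infer:

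- **That 34 is miscalculated.** It reproduces. The fault is the model.
- **That counting the pilot children creates the power problem.** It does not, since about 140 also exceeds 34.
- **That the protocol conceals the cluster limitation.** It discloses it twice.
- **That classroom-level analysis shows a shortfall throughout.** At classroom ICC 0.05 the detectable 0.92 SD is smaller than the planned 1.0 SD. Only at 0.10 (1.14 SD) is it larger.

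The reply does not rescue the 80% figure. The calculation is presented as the one for the comparative phase, and that phase has no between-kindergarten degrees of freedom. Saying that few clusters may constrain power understates this. A low assumed ICC does not help either, because the design-effect figures presuppose a known variance that the trial cannot estimate.

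**Conclusion.** The point holds. The stated 80% power belongs to a trial of independently randomised children, not to this one. The decisive reason needs no particular ICC: with one kindergarten per arm, treatment and kindergarten are fully confounded, and for any kindergarten ICC above zero no number of children supports an 80% power claim.

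The design-effect figures are a favourable illustration. They show the main-phase sample worth fewer than the 34 required once the ICC exceeds about 0.045. They rest on an assumed ICC, an equal split and no dropout. The pilot-inclusive comparator is a secondary wording error. Because the statement concerns the primary comparison and is wrong for the design, it should be corrected before the comparative phase is reported.

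**What to change.** - In Sample size, delete "The overall recruited sample exceeds this individual-level requirement". In the strengths and limitations list, delete "despite an adequate individual-level sample size".
- State the main-phase sample: about 140 children, 6 classrooms, 2 kindergartens.
- Say that 34 holds only for independent children and that 80% power is not claimed for the kindergarten-randomised comparison. Null and significant results alike should be read as estimates confounded with kindergarten.
- If a table of detectable differences over an assumed ICC range is added, label it illustrative. A classroom-level version must state that it assumes no between-kindergarten variance, and should set its values (about 0.92 SD at ICC 0.05, 1.14 SD at 0.10) beside the planned 1.0 SD of change.
- Do not lean on the pilot for the ICC. Four classrooms in one kindergarten give at most a rough classroom ICC and no kindergarten ICC.

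The cost is one rewritten paragraph, one shortened sentence and a less favourable stated figure. No extra children are needed. Rewording makes the claim honest; it does not remove the confounding, which comes from having one kindergarten per arm.

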### Data analysis

Data analysis will be conducted using an integrative mixed-methods approach, combining quantitative and qualitative data, and will be performed separately for the pilot phase and the main study phase.

For the pilot phase, feasibility and acceptability indicators will be analysed descriptively, including recruitment, retention and attendance rates, as well as indicators related to implementation, resources and safety. Preliminary changes between baseline and postintervention will be explored using within-group comparisons, as appropriate.

For the main study phase, quantitative outcomes will be analysed by comparing the intervention and wait-list control groups at baseline and postintervention. The choice of statistical tests will be guided by the distribution and characteristics of the data. Where assumptions for parametric analyses are not met, non-parametric tests will be used to compare baseline differences between groups and changes from baseline to postintervention between groups.

Effect sizes will be calculated and reported to support interpretation of findings. The specific metric used will depend on the statistical tests applied, and effect sizes will be interpreted according to established guidelines. Results will be presented as means and SDs or means and 95% CIs, as appropriate.

All statistical analyses will be conducted using a significance level of p<0.05.

Qualitative data, including interviews and observational data, will be analysed using thematic analysis, and findings will be integrated with quantitative results to support interpretation of feasibility, acceptability and intervention effects.

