**Methods and analysis:**

This study describes the protocol of a cluster-randomised trial to be conducted in Portugal, involving three kindergartens and up to 215 preschool children, their educators and parents. The protocol includes an initial pilot phase (approximately 75 children from one kindergarten) to assess feasibility, acceptability and implementation procedures, followed by a main study phase with intervention and wait-list control clusters. The intervention comprises 15 sessions delivered in outdoor kindergarten settings. PLAY UP adopts a multidimensional and multimethod approach combining quantitative and qualitative methods. Outcomes related to physical literacy, including physical activity, motor competence, engagement, enjoyment and motivation for movement, are assessed using questionnaires, standardised tasks, accelerometry, Global Positioning System-based positioning technologies and systematic observations, complemented by interviews. Data will be analysed using cluster-aware statistical models and integrative mixed-methods approaches.

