Prior to the intervention, outdoor affordances for play, including physical, social and risk affordances, will be identified and categorised based on data collected using the Go-Exterior instrument and participatory methods (Photo Elicitation Interviews, PEI). This process enables the identification of environmental features that support active play and engagement, and risky play (eg, a flat open area affording running and jumping; a tree affording climbing and risk-taking).^14 40 41^

The intervention is developed and implemented through a co-creation approach, actively involving children in shaping play experiences. Children’s input, gathered through PEI and observational data, informs session design, selection of materials and equipment, identification of preferred and underused play areas, and recognition of PA versus sedentary behaviour (SB) zones, as well as social interaction spaces. This approach supports the prioritisation of meaningful play areas and encourages the exploration of less-used environments.

The research team comprises members with expertise in the design and implementation of interventions for preschool children in both indoor and outdoor contexts.^15 23 42^ Sessions will be delivered by a psychomotor therapist under weekly supervision by the principal investigator (PI), who has expertise in psychomotor practice and supervision.

The intervention consists of 15 outdoor sessions (60 min each), delivered twice weekly and integrated into the regular preschool routine involving the whole class. Sessions are led, as mentioned above, by a psychomotor therapist professional, with the classroom educator providing pedagogical support through a non-intrusive presence. This approach ensures safety, supports engagement in outdoor exploration, and promotes meaningful learning experiences.^13 15^ Each session follows a semistructured format,^15^ organised into three main components:

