Sessions are conducted in outdoor KG environments, leveraging natural and built features that afford opportunities for movement and social interaction. To enrich play experiences, the environment will be supplemented with portable equipment (eg, balls, hoops), loose parts, and natural and recyclable materials (eg, cardboard boxes, tyres, paper tubes, textiles). These materials will remain available after the intervention to support continued engagement in outdoor active play. Activities are tailored to children’s developmental characteristics (eg, age, height, competencies) and informed by behavioural and contextual data, including CLPI, SAB and environmental assessments.

Given the outdoor nature of the intervention, contingency measures will be implemented to address weather-related challenges. To ensure continuity of sessions under adverse conditions (eg, rain or muddy environments), appropriate equipment (eg, waterproof boots, overalls and rain jackets) will be provided.

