
### Outcomes and measures

Outcomes will be assessed using a multidimensional and multimethod approach, combining objective measures, standardised assessments and qualitative data, as summarised in table 1.

**Table 1 T1:** Overview of outcomes and measures used in the PLAY UP study, including primary, secondary and process outcomes, corresponding instruments, respondents and assessment time points (baseline and postintervention)

Outcome category	Outcome	Measure/instrument	Respondent/source	Time point
Primary outcome	Motor competence	Movement Assessment Battery for Children–Second Edition	Child	T0, T1
Secondary outcomes	Social, emotional and behavioural competences	Preschool and Kindergarten Behaviour Scales	Educator	T0, T1
	Behavioural difficulties	Strengths and Difficulties Questionnaire	Parent	T0, T1
	Executive functioning	Head-Toes-Knees-Shoulders Task	Child	T0, T1
	Spatial Activity Behaviour	Accelerometry+GPS	Child	T0, T1
	Child-Level Positional Interactions	Sensor-based positional tracking	Child/group level	T0, T1
	Kindergarten Affordances for Physical Literacy	Go-Exterior + Photo Elicitation Interviews	Research team/educators/children	T0, T1
Process outcomes (pilot phase)	Feasibility	Recruitment, retention, participation, attendance, adherence	Children, educators, research team	Pilot phase
	Acceptability	Observational records and interviews	Children, educators, research team	Pilot phase
	Implementation quality	Dose, intensity, duration, fidelity, resources, barriers/facilitators and safety	Educators, research team	Pilot phase

GPS, Global Positioning System; T0, baseline/initial assessment; T1, postintervention assessment.

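### The abstract promises cluster-aware models, but the Data analysis section names none and chooses two-group tests by distribution, which points to standard errors that ignore classroom clustering

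*Protocol article*

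**What the plan says.** All references are to the protocol article.

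- **Abstract, Methods and analysis:** "Data will be analysed using cluster-aware statistical models and integrative mixed-methods approaches".
- **Data analysis:** the two arms are compared at baseline and postintervention. The rule for the method is "The choice of statistical tests will be guided by the distribution and characteristics of the data". The fallback is "Where assumptions for parametric analyses are not met, non-parametric tests will be used to compare baseline differences between groups", and the same sentence extends it to between-group change. The threshold is p<0.05 for everything. No cluster, classroom or random-effect term appears.
- **Study design:** "This study is a cluster-randomised trial, with randomisation at the kindergarten (KG) level". For the comparative phase, "the intervention will be implemented in the remaining two clusters (three classrooms each), with one assigned to the intervention condition"; the other kindergarten is the wait-list control. That gives one kindergarten and three classrooms per arm.
- **PLAY UP intervention programme (children's approach):** sessions are "integrated into the regular preschool routine involving the whole class".
- **Sample size:** a G*Power repeated-measures ANOVA (within–between interaction) gives 34 children, with no ICC or design effect. The text itself calls this an individual-level requirement. It adds that effects will be interpreted cautiously and reported with confidence intervals.
- **Table 1:** the secondary outcomes at T0 and T1 include "Kindergarten Affordances for Physical Literacy", measured with Go-Exterior and photo interviews, and Child-Level Positional Interactions (CLPI), labelled as child or group level.

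**The concern.** The abstract and the operative section give different rules for the analysis, and nothing in the article reconciles them. This is more than a detail left to an analysis plan. The Data analysis section states how the method will be chosen, and the criterion is the distribution of the data, not its clustered structure. An analysis plan that followed that section would break the promise in the abstract.

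Children in one class share sessions, an educator and a playground, so their outcomes, or their changes, may be correlated. If the tests treat them as independent, the p-values and confidence intervals for the primary outcome (MABC-2 total score) and the other child-level outcomes overstate precision. The Sample size section offers those same intervals as a basis for planning future studies, so the error would be passed on.

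A secondary matter concerns two outcomes in Table 1. Go-Exterior rates the outdoor setting, and the intervention supplies that setting with materials: "These materials will remain available after the intervention to support continued engagement in outdoor active play". Mean inter-child distance, one of the CLPI outcomes, is determined jointly by the children present in a recess. Neither yields independent child-level observations.

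**Working it through.** **1. The plan's own sample size.** For the within–between interaction, λ = f²·N·m/(1−ρ), with df 1 and N−2. The inputs from Sample size are f = 0.25, m = 2 occasions, ρ = 0.50 and α = 0.05. At N = 34, λ = 0.0625 × 34 × 2/0.5 = 8.5 and power is 0.807. At N = 32, power is 0.781. So 34 is the smallest even total that reaches 0.80, and the stated figure reproduces. It does so with children as independent units and no allowance for clustering.

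**2. Could the fallback work on classroom means?** With three classrooms against three there are 20 possible rank allocations, so the smallest two-sided p is 2/20 = 0.10. A standard rank-sum test can reach the stated p<0.05 only if children are the units. Steps 1 and 2 make a child-level analysis the natural reading, although the section does not use that term.

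**3. Cluster size.** Recruitment gives 215 children and Study design puts about 75 in the pilot. That leaves 215 − 75 = 140 in six classrooms, or 140/6 = 23.3 each.

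**4. Effect of ignoring classrooms.** The article gives no ICC, so a range is assumed. It refers to the score or change actually analysed.

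- Design effect: DE = 1 + 22.3 × ICC.
- Standard error too small by √DE.
- True type I error = 2·(1 − Φ(1.96/√DE)).
- Confidence interval ratio = √DE × 2.78/1.98. Here 2.78 is the t critical value on 4 df (six classrooms less two arms) and 1.98 the value on 138 df.

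| Assumed ICC | DE | SE factor | Type I error | 95% CI should be wider by |
|---|---|---|---|---|
| 0.01 | 1.22 | 1.11 | 7.6% | about 1.55 |
| 0.05 | 2.12 | 1.45 | 17.8% | about 2.0 |
| 0.10 | 3.23 | 1.80 | 27.6% | about 2.5 |

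**5. Check by simulation.** Three classrooms per arm of 23, 23 and 24 children were simulated with no true effect and no kindergarten variance (20,000 runs; 4,000 for Mann–Whitney).

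| ICC | Child-level t-test | Mann–Whitney | t-test on six classroom means |
|---|---|---|---|
| 0 | 4.9% | 4.6% | 5.0% |
| 0.05 | 18.2% | 18.3% | 5.3% |
| 0.10 | 28.1% | 26.3% | 5.1% |

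Choosing a non-parametric test does not help. Using the classroom as the unit does, as far as classroom clustering goes.

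**6. What a classroom-level analysis cannot reach.** With about 70 children in the single kindergarten of each arm, an ICC acting at kindergarten level gives DE = 1 + 69 × ICC. That is 1.69 at 0.01 and 4.45 at 0.05, with type I errors of about 13% and 35%. One kindergarten per arm leaves this variance inestimable.

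**The case against.** The strongest reply is that the Data analysis section never says clustering will be ignored. It refers to the characteristics of the data as well as their distribution, and Patient and public involvement mentions a statistical analysis plan that is not shown, where model terms normally sit. This stands in part. A reader might infer that the article states a child-level analysis. It does not: that reading is an inference from the two-group test wording, the individual-level sample size and the 0.10 floor of a classroom rank test. The inconsistency with the abstract does not depend on that inference.

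Other stronger readings are not supported:

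- **That every p-value and interval will be wrong.** This needs an ICC above zero. At zero the child-level t-test holds its level (4.9%). Where change is compared, a constant rating bias of an educator on the behaviour scale cancels, so a shared rater does not by itself prove clustering of change.
- **That Go-Exterior must rise because equipment is left behind.** The instrument also covers matters such as accessibility, maintenance and safety, and adult role, and its items are not reproduced. The text supports only that part of the score can be affected by supplied materials. No between-arm test of Go-Exterior is specifically planned; the general wording on quantitative outcomes merely does not exclude it.
- **That CLPI is not child-level at all.** Table 1 labels it child or group level, and proximity interactions can be counted per child. The point is dependence, clearest for mean inter-child distance.

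The article also discloses the small number of clusters and promises caution. That limits the claims, but it does not alter a standard error.

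**Conclusion.** The point holds as an unreconciled inconsistency in how the primary and other child-level outcomes will be analysed. Followed as written, and on its natural reading, the Data analysis section would understate standard errors whenever the classroom ICC is above zero. The table in the working gives the size for ICCs of 0.01 to 0.10. Those figures rest on assumed ICCs, roughly equal classrooms of 23, and no kindergarten-level variance. They are therefore illustrations over a range, not estimates for this trial.

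A reader might also infer that a classroom-clustered model would make the comparison sound. It would not. Arm and kindergarten are completely confounded, and the corrected intervals would still omit between-kindergarten variance. The point on Go-Exterior and inter-child distance is secondary and concerns reporting.

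**What to change.** In Data analysis, replace the sentences on choosing tests by distribution with one stated model for child-level outcomes that delivers what the abstract promises. One suitable choice is a linear mixed model of the T1 score on arm and T0 score, with a classroom random intercept and Kenward–Roger or Satterthwaite degrees of freedom (about 4). An equivalent analysis of the six classroom means on 4 df would also serve.

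Add a plain statement that, with one kindergarten per arm, no model removes kindergarten confounding, that the intervals omit between-kindergarten variance, and that the comparison is exploratory.

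Report Go-Exterior descriptively, and do not test mean inter-child distance as independent child-level data.

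A permutation test over classrooms should not be offered as a check. Classrooms were not the randomised units, and its p-value cannot fall below 0.10.

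**Cost:** wording and a standard model, with no new data. Intervals become wider and apparent power falls. At the planned f = 0.25 and ρ = 0.50 with 140 children, λ = 0.0625 × 140 × 2/0.5 = 35, and the child-level calculation gives power above 0.99. Dividing λ by the design effect and using 4 df gives about 0.97, 0.85 and 0.70 at classroom ICCs of 0.01, 0.05 and 0.10, still without kindergarten variance.
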